### Randomisation

This will be performed using a centralised validated computer randomisation programme through a secure (encrypted) web-based service, provided by the Oxford Clinical Trials Research Unit (OCTRU). Eligible participants will be randomised when they receive a date for their SARS-CoV-2 booster vaccination. The randomisation system will stratify on whether the participant is on their first line or subsequent line of therapy for CLL to ensure balanced allocation across treatment groups. It will use a 1:1 ratio to allocate to either continuing taking BTKi as usual or to have a 3-week pause (1 week before and 2 weeks after their booster vaccination against COVID-19).

Randomisation will be stratified on the line of CLL therapy being used as it has already been shown that the magnitude of immune response differs depending on the number of lines of therapy.^27^ We have chosen not to stratify on past COVID-19 infection even though it is a strong modifier of serological response to SARS-CoV-2 vaccines as it is difficult to ascertain this reliably from participant self-report. We are also not stratifying on the first vaccine platform received (eg, adenovirus vector or mRNA) as we have previously shown that there is no difference in the magnitude of antibody response by vaccine platform in patients with CLL,^27^ nor on which BTKi therapy the participant is currently taking. However, we will obtain past infection status using anti-nucleocapsid antibodies and use this in the statistical analysis. Due to the nature of the intervention, the participants and the clinical team will not be blind to the allocated arm of the study. However, those analysing the study samples will be blinded to the participants’ allocation. Trial statisticians will not be blinded.

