### Sample size and justification

A total of 120 participants will be randomised. The sample size estimates were based on the anti-spike-RBD response after vaccination dose from a small observational study of patients with CLL who were either taking or not taking BTKi.^27^ This suggested a large suppressive effect of BTKi (effect size of 0.9SD). However, anti-spike RBD response related to booster vaccination in CLL patients suggests a smaller though still large effect is more plausible (circa 0.7 SD). Conservatively, we have based the sample size calculation on an effect size of 0.65SD (detecting at least a 0.97 unit (log10 scale) higher antibody response in the BTKi suspension group with 90% statistical power at two-sided 5% significance level which requires data from 102 participants. This leads to 120 participants after allowing for 15% missing data. This calculation was performed using the Stata V.15.1 ‘power twomeans’ command.

Statistical analysis: Full details will be presented in a separate statistical analysis plan which will be drafted and finalised and aimed to be published prior to the final analysis data lock and will receive review and input from the trial steering committee (TSC) and data monitoring committee. The principal analysis will be performed on the as randomised (‘intention-to-treat’) population, analysing participants with available outcome data in their randomised groups, regardless of adherence. The study will be reported in line with Consolidated Standards of Reporting Trials guidelines.^35^

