The primary objective of the statistical analysis will be to identify if a temporary 3-week pausing of BTKi around the time of vaccination against SARS-CoV-2 increases the anti-spike-RBD antibody at 3 weeks postvaccine compared with continuing BTKi treatment without interruption. The anti-spike-RBD antibody levels will be summarised descriptively at baseline and 3 and 12 weeks post-COVID-19 booster vaccination follow-up. The differences between the study arms will be estimated using a mixed effects regression model, allowing for repeated measures clustered within participants. The model will be adjusted for a randomisation factor (first line or subsequent line of therapy), and prior infection status obtained from prevaccination antinucleocapsid antibodies, as fixed effects. A treatment by time interaction will be included. The model is anticipated to use an unstructured covariance matrix, and maximum likelihood estimation. Data will be log-transformed prior to analysis, as appropriate. The adjusted mean difference between the groups will be presented, together with 95% CI and p values. The regression model will be simplified (eg, linear regression) if the planned model does not converge.

Supplemental analyses will explore the time effect between the last COVID-19 vaccination dose and the dose given in IMPROVE. The effect of non-compliance to the randomised intervention will be explored using per-protocol analyses.

The same model as for the primary outcome will be used to analyse the 12-week PVB anti-spike-RBD antibody outcome. Similar supportive analyses as planned for the primary outcome will be performed for 12 weeks PVB data. Overall, 50% and 90% neutralisation by Wuhan and VOC along with, T cell spike response by subtype (spike for Wuhan and VOC, and nucleocapsid and membrane), will be analysed in a similar manner to anti-spike RBD antibody outcome. Other secondary outcomes will be analysed using generalised linear models for binary and continuous data, as appropriate, with model adjustment as described above.

The number of SAEs will be presented by treatment arm. The proportion of participants with at least one SAE will be compared. Details of the events will be presented, together with information on the timing of the events from randomisation.

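### The primary repeated-measures model names maximum likelihood as its anticipated estimator; at this sample size that makes the standard error about 2% too small, a minor anti-conservative effect that REML with small-sample degrees of freedom removes at no real cost.

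*Protocol article*

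**What the plan says.** The statistical analysis text sits under 'Sample size and justification' in the protocol article. The arms are compared with a mixed effects model for repeated measures within participants, with a treatment by time interaction. On covariates: "The model will be adjusted for a randomisation factor (first line or subsequent line of therapy), and prior infection status obtained from prevaccination antinucleocapsid antibodies," both as fixed effects. On estimation: "The model is anticipated to use an unstructured covariance matrix, and maximum likelihood estimation". The model may be simplified, for example to linear regression, if it does not converge. An adjusted mean difference with 95% confidence interval and p value is to be reported. No degrees-of-freedom method or reference distribution is named.

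The 12-week antibody outcome uses the same model, and the neutralisation and T-cell outcomes are analysed in a similar way.

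The trial is sized for "90% statistical power at two-sided 5% significance level which requires data from 102 participants", and 120 are to be randomised. Full analysis details are left to a separate statistical analysis plan, due before the final data lock.

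**The concern.** ML estimates the covariance matrix by dividing residual sums of squares and products by the number of participants. It does not subtract the degrees of freedom used by the fixed effects, so variances and standard errors are biased downward. REML makes that subtraction. If Wald statistics are also referred to the normal distribution, uncertainty in the variance estimate is ignored as well, which adds a second, smaller error in the same direction.

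At stake is the calibration of the p value and confidence interval for the single primary comparison, which is meant to be tested at a two-sided 5% level. Because the secondary immunological outcomes follow the same approach, the choice carries over to them. The article names the estimator, so this is a stated choice that can be assessed, not a detail left open.

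**Working it through.** **1. The plan's own figure.** Inputs from 'Sample size and justification' and 'Randomisation': effect 0.65 SD (0.97 log10 units, so implied SD 0.97/0.65 = 1.49), two-sided 5%, power 90%, 1:1 allocation, 15% missing. A two-sample t-test calculation with the noncentral t gives 51 per arm, 102 in total, with power 0.902. Then 102/0.85 = 120. Both stated figures reproduce.

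**2. Inputs for the check.**
- Participants N: 102 (evaluable target) or 120 (all randomised).
- Mean parameters per time point p: 4, for the visit mean, the arm effect, line of therapy and prior infection. With baseline antibody as a covariate, p = 5; that is an assumption, since the article does not say how baseline enters.
- Reference distribution: not stated, so t and normal are both shown.

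**3. Formulas.** These treat the week-3 comparison as a cross-sectional regression with ν = N − p.
- Ratio of ML to REML standard error: r = √((N − p)/N).
- Type I error, ML with t reference: 2·P(T_ν > r·t_{0.975,ν}).
- Type I error, ML with normal reference: 2·P(T_ν > 1.96·r).
- Interval width, ML with normal relative to REML with t: 1.96·r / t_{0.975,ν}.

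Worked case, N = 102 and p = 4: r = √(98/102) = 0.980 and t_{0.975,98} = 1.984. ML with t has an effective cut-off of 0.980 × 1.984 = 1.945, so type I error is 5.46%. ML with normal has a cut-off of 0.980 × 1.960 = 1.921, so type I error is 5.76%. The width ratio is 1.921/1.984 = 0.968.

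| N | p | r | ML, t | ML, normal | REML, normal | Width ratio |
|---|---|---|---|---|---|---|
| 102 | 4 | 0.980 | 5.46% | 5.76% | 5.28% | 0.968 |
| 102 | 5 | 0.975 | 5.58% | 5.89% | 5.29% | 0.963 |
| 120 | 4 | 0.983 | 5.39% | 5.64% | 5.24% | 0.973 |
| 120 | 5 | 0.979 | 5.49% | 5.75% | 5.24% | 0.969 |

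The inverse width ratios, 1.028 to 1.038, give the widening from the correction: about 3 to 4%.

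**4. Simulation.** An unstructured ML repeated-measures model was simulated under the null, with 6,000 replicates per scenario (Monte Carlo standard error about 0.3 percentage points). Assumptions not in the article: visit correlations 0.6 to 0.8, prior infection in 60%, normal reference. The corrected column rescales the statistic for 5 mean parameters and uses a t reference, as a stand-in for REML with small-sample degrees of freedom.

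| Scenario | ML, normal | Corrected |
|---|---|---|
| 120, 15% missing per follow-up visit, baseline as outcome | 5.5% | 4.8% |
| 120, 15% missing per follow-up visit, baseline as covariate | 5.6% | 4.8% |
| 102 complete, baseline as outcome | 5.5% | 4.8% |
| 102 complete, baseline as covariate | 5.8% | 5.0% |

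Within Monte Carlo error, the simulation agrees with the formulas in direction and size.

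**5. What it could change.** At N = 102 and p = 4, a corrected p value of exactly 0.05 would appear under ML with a normal reference as 2·P(Z > 1.984/0.980) = 0.043; with p = 5 it would appear as 0.042. Only results reported between about 0.042 and 0.05 would change sides.

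**The case against.** The case against has four parts.

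- **The wording is provisional.** A reader might infer that the primary analysis is locked to ML. The text only anticipates it and leaves full details to the statistical analysis plan. That stands: ML is named, not fixed.
- **The reference distribution is not given.** Degrees of freedom are commonly left to the analysis plan, so their absence here is no fault, and the 5.6 to 5.9% range rests on an assumed normal reference. That also stands. It does not remove the point, because ML alone, even with a t reference, gives 5.4 to 5.6%.
- **Less favourable settings.** Eight parameters at N = 102 would give 6.3%, but the covariates listed supply only 4, or 5 with baseline, at the week-3 comparison. The larger figure should not be used.
- **The effect is immaterial.** ML is a legitimate, asymptotically valid estimator, and an excess below one percentage point matters only near the threshold. This is right about size and is why the priority is low. It is no reason to keep the less well-calibrated option when the alternative is free.

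**Conclusion.** The point holds as a minor one. ML, as named, gives a standard error about 2% too small. Type I error is about 5.4 to 5.6% with a t reference and about 5.6 to 5.9% with a normal one; in the latter case the 95% confidence interval is about 3 to 4% too narrow. This rests on 102 to 120 participants and 4 to 5 mean parameters per time point; the upper range also needs the assumed normal reference.

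A reader might go further and conclude that control of the 5% error rate is lost, or that the sample size is undermined. The documents support neither. The excess is under one percentage point and depends partly on a choice the article does not state, and 102 and 120 reproduce exactly.

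**What to change.** In the statistical analysis text of the protocol, and in the statistical analysis plan, replace the reference to ML with: restricted maximum likelihood (REML) estimation with Kenward-Roger or Satterthwaite degrees of freedom. Apply the same to the 12-week antibody, neutralisation and T-cell models.

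Both parts help: REML with a normal reference would still give about 5.2 to 5.3%. The cost is one phrase and a different option in the model-fitting command, with no extra data or participants and no change to the sample size. The interval becomes about 3 to 4% wider than under ML with a normal reference. The analysis plan is due before the final data lock, so the change can be settled there.

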#### Control arm

To continue the same dose and regimen of BTKi therapy as usual in the week before and weeks after receiving the booster vaccination against COVID-19.

No concomitant care or interventions are prohibited in the study and the participants’ clinical care team will continue to manage their condition in the usual way after the end of their participation in the study.

Automatic reminders by Short Message Service (SMS) or email will be sent to participants to encourage adherence to their randomised intervention, where they consent to receive these. Participants may be telephoned by the study team if they decline the use of SMS or emails for reminders.

Participants and their usual care team will be able to manage any potential tumour flares including with steroids or any other drug as clinically appropriate. Should a clinical need arise, the participants’ usual care team will be able to advise them to continue or not with their allocation. It is known that tumour flare is fully reversible with the reintroduction of BTKi,^25^ and planned dose suspensions are common and do not appear to compromise long-term outcomes such as progression free or overall survival.^31^

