#### Secondary outcomes

Levels of anti-spike RBD antibody at 12 weeks PBV.Participant assessments of disease activity: global assessment using a Numeric Rating Scale (NRS) with 1-week recall at baseline, 3 and 12 weeks PBV, current disease activity level and change since baseline, 3 and 12 weeks PBV.Disease flare-up (tumour flare) and actions taken to deal with them at 3 and 12 weeks PBV.Effect on QoL (assessed using European Organisation for Research and Treatment of Cancer -Quality of Life Questionnaire (EORTC-QLQ-CLL17)) at 3 and 12 weeks PBV.Adherence with advice to pause or continue BTKi: self-report at 3 weeks PBV.COVID-19 neutralising titre at baseline and 3 weeks PBV.T cell responses against ancestral Wuhan and the latest variant of concern (B1, B4, B5 and Sanofi) at baseline and 3 weeks PBV.

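### Non-compliance is explored only by per-protocol analyses, although departure from allocation may follow disease status; a complier-average causal effect should be added and take precedence

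*Protocol article*

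**What the plan says.** The statistical analysis text, printed under Sample size and justification, makes the principal analysis as randomised, "analysing participants with available outcome data in their randomised groups, regardless of adherence". Among the supplemental analyses it adds: "The effect of non-compliance to the randomised intervention will be explored using per-protocol analyses". Similar supportive analyses are planned for the week-12 antibody level. The per-protocol set is not defined, and full detail is left to a separate analysis plan.

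The text under Control arm, which also covers management in the trial generally, says: "Should a clinical need arise, the participants’ usual care team will be able to advise them to continue or not with their allocation". It continues: "It is known that tumour flare is fully reversible with the reintroduction of BTKi". It allows flare to be managed with steroids or other drugs.

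Secondary outcomes lists the adherence measure: "Adherence with advice to pause or continue BTKi: self-report at 3 weeks PBV".

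**The concern.** A per-protocol set selects on something that happens after randomisation. That is harmless only if those who depart from allocation have the same expected outcome as those who do not. Here the article describes a route by which departure can follow clinical need. Flare is the obvious example in the pause arm, because it is said to resolve when BTKi is reintroduced. If flare is related to underlying disease status, and disease status to antibody response, the adherent participants left in one arm are no longer comparable with those left in the other. The result then mixes the effect of non-compliance with selection.

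The per-protocol result could well be read closely. If restarters gained nothing and 20% restarted (an assumption), the as-randomised effect would fall from the design value of 0.65 SD to 0.65 × 0.80 = 0.52 SD. Readers of a borderline result would then look to the non-compliance analysis to judge a pause that was kept to.

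**Working it through.** **Inputs from the article (Sample size and justification).** Effect 0.65 SD, equal to 0.97 log10; 90% power; two-sided 5%; 102 evaluable; 15% missing; 120 randomised. Implied SD = 0.97 / 0.65 = 1.49 log10.

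**Inputs assumed.** Share f of the pause arm restarting early; the strength of the link between disease status and restart; the correlation ρ between disease status and log titre; the share of benefit kept by restarters. The article gives none of these.

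**1. The plan's own figures.** Two-sample t-test, noncentral t: 51 per arm gives power 90.2%, so 102 in total. 102 / 0.85 = 120. Both reproduce, and this point does not affect them.

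**2. Selection bias under no true effect.** Let U be disease status in SD units (higher is better) and let log titre in SD units be ρU plus independent noise. The probability of restart is logistic in U with slope −1, so the odds rise by a factor of e per SD of worse disease. The intercept is set to give the chosen f. With the control arm complete, per-protocol bias = ρ × E(U | no restart) × 1.49. At ρ = 0.3:

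| f | E(U given no restart) | Bias, SD | Bias, log10 | Ratio |
|---|---|---|---|---|
| 5% | 0.047 | 0.014 | 0.021 | 1.05 |
| 10% | 0.091 | 0.027 | 0.041 | 1.10 |
| 20% | 0.173 | 0.052 | 0.078 | 1.20 |
| 30% | 0.253 | 0.076 | 0.113 | 1.30 |

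At ρ = −0.3 each bias changes sign.

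**3. Scale.** The standard error of the difference with 51 per arm is 1.49 × √(2/51) = 0.295 log10. The 20% figure is 0.078 / 0.295, about a quarter of one standard error, and 0.078 / 0.97 = 8% of the design difference.

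**4. A stronger link.** Let ρ instead be the correlation between titre and the restart liability itself, with restart above a threshold. At |ρ| = 0.3 the bias is 0.03, 0.06 and 0.11 SD at f = 5%, 10% and 20%. Against a true 0.65 SD, per-protocol returns 0.71 or 0.59 at 10%, and 0.76 or 0.55 at 20%, depending on sign. Under no effect, the nominal 5% test rejects in 5.9% of trials at f = 10% and 7.8% at f = 20%. At ρ = 0.5 these become 7.6% and 13.1%.

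**5. The alternative.** The complier-average causal effect is the intention-to-treat difference divided by the between-arm difference in exposure. Under no effect the numerator has expectation zero, so this selection bias does not arise. For a true full-pause effect of 0.65 SD:
- Restarters keep no benefit: 0.65(1 − f) / (1 − f) = 0.65 at any f and ρ.
- Restarters keep half the benefit, exposure coded yes/no: 0.6175 / 0.90 = 0.69 at f = 10%, and 0.585 / 0.80 = 0.73 at f = 20%. This overstates the effect.
- Same case, exposure graded by days off BTKi and benefit proportional to it: 0.6175 / 0.95 = 0.65 and 0.585 / 0.90 = 0.65.

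**The case against.** **Direction.** A reader might infer that the per-protocol result must favour pausing. The documents do not support that: nothing in the article links flare or restart to antibody titre, and the sign of the bias follows the sign of an assumed correlation.

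**One arm only.** A reader might also infer that only pause-arm participants would be dropped. Adherence is recorded for both instructions, the clinical-need clause is not confined to one arm, and the Introduction says that pausing CLL therapy is not uncommon. Control-arm departures are possible. The per-protocol set is also undefined, so a clinically advised restart might count as within protocol, in which case nobody would be excluded for it. These points stand. They limit the claim to a bias that can arise.

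**Importance.** The analysis is supportive and exploratory, and the primary analysis ignores adherence. Eligibility requires at least 12 months on BTKi, disease in remission or stable, and a judged ability to pause safely; reminders are sent. A 20% or 30% restart rate may therefore be high. This stands too and keeps the point modest.

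**The remedy has its own bias.** With a yes/no exposure, partial pauses breach the exclusion restriction, and the resulting error (0.69 and 0.73 for 0.65) is about as large as the per-protocol bias under the stronger link. Steroids given for flare are another route from allocation to titre. This is a fair criticism of a yes/no instrument used alone, and the reason to prefer a graded exposure. It does not rescue per-protocol as the sole method: the complier estimate keeps every randomised participant with outcome data in the allocated arm and is free of this selection bias when there is no effect.

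**Conclusion.** The point holds in a limited form. The article names per-protocol as the only way of exploring non-compliance while describing a route by which adherence may depend on disease status. Excluding non-adherent participants can therefore bias that comparison, in a direction that cannot be known beforehand. Under the assumptions in step 2 with no true effect, the spurious difference is about 0.04 log10 (1.10-fold) at 10% restarts and 0.08 log10 (1.2-fold) at 20%. The size rests wholly on assumed inputs and is small beside the standard error. The primary analysis and the sample size are untouched. This is an improvement to a supportive analysis that is worth making before data lock.

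**What to change.** In the analysis plan, add to the non-compliance analyses at weeks 3 and 12 a complier-average causal effect:
- Randomised arm as instrument, with the primary-model covariates (line of therapy and prior infection status).
- Exposure as days off BTKi in the planned window where the week-3 adherence record allows; completed pause (yes/no) otherwise.
- Precedence for this estimate when describing the effect of an adhered-to pause. Define the per-protocol set, state how a clinically advised departure is classed, and label any per-protocol result descriptive.
- A statement of the exclusion restriction and monotonicity, noting that partial pauses under a yes/no exposure, and steroids given for flare, may strain them.

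Cost: a few sentences and a few lines of code. Adherence is already collected at week 3, although the article does not say whether days off BTKi are recorded. The confidence interval will be wider than under per-protocol, and the estimate still relies on self-report. Nothing here bears on when BTKi should be restarted.

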**Methods and analysis:**

An open-label, randomised controlled superiority trial will be conducted in haematology clinics in approximately 10 UK National Health Service (NHS) hospitals. The sample size is 120, randomised 1:1 to intervention and usual care arms. The primary outcome is anti-spike-receptor binding domain (RBD) antibody level at 3 weeks post-SARS-CoV-2 booster vaccination. Secondary outcomes are RBD antibody levels at 12 weeks postbooster vaccination, participant global assessments of disease activity, blood films, full blood count and lactate dehydrogenase levels, impact on quality of life, self-reported adherence with request to temporarily pause or continue BTKi, T cell response against spike protein and relative neutralising antibody titre against SARS-CoV-2 viral variants. Additionally, there will be an investigation of any effects in those given influenza vaccination contemporaneously versus COVID-19 alone.

The primary analysis will be performed on the as randomised groups (‘intention to treat’). The difference between the study arms in anti-spike-RBD antibody level will be estimated using a mixed effects regression model, allowing for repeated measures clustered within participants. The model will be adjusted for randomisation factor (first line or subsequent line of therapy), and prior infection status obtained from prerandomisation antinucleocapsid antibodies as fixed effects.

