We hypothesise that people taking BTKi specifically Ibrutinib or Acalabrutinib for their CLL at the time of vaccination against COVID-19 (±an influenza vaccination) will have an impaired immune response to the vaccine dose, and therefore, lower production of anti-spike-receptor binding domain (RBD) and neutralising antibodies. We propose that a 3-week pause in BTKi treatment will improve the vaccine-specific immune response, without significant worsening of the control of the underlying CLL, when compared with continuation of treatment as usual. The design and delivery of this study was based around another trial that assessed pausing the immune suppressant drug methotrexate around the time of COVID-19 vaccination in patients with inflammatory disorders.^24^ Pausing of CLL therapy is not uncommon and is recommended perioperatively due to the off-target effect of BTKi therapy on platelet function, which results in an increased bleeding risk.^25 26^ Individuals can then experience a disease flare (which can include enlargement of lymph nodes and/or “B symptoms”, such as fever, sweats and weight loss); most are mild with symptoms such as a fever, rash or mild pain, but some can experience raised lymphocyte counts, enlarged spleens, and pain and changes seen in their blood biochemical profiles.

Currently, no randomised trials have examined the impact of pausing BTKi therapy in patients with CLL for vaccine responsiveness. However, several observational studies have shown poorer responses in those taking BTKi and in addition, improvement in responses off therapy. In the CLL-VR study, following the second dose of vaccine, response rates were almost half in patients who took a BTKi compared with healthy controls.^27^ Greenberger *et al* studied responses to a third dose of COVID-19 vaccination in 25 patients with CLL, 13 of whom were treated with BTKi. Of these, 6/13 had an elevated anti-Spike response but 4 had stopped therapy and one was maintained on a low dose. In comparison, among those who continued therapy, five had a very weak response (<5.2 U/mL) and two had an intermediate response (<250 U/mL).^28^ These data suggest that both the proportion of responders and the strength of response increases in patients not taking BTKi therapy.

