Thus, the main aim of this study is to assess whether a 3-week pause in BTKi treatment, 1 week before and 2 weeks after SARS-CoV-2 vaccine booster, improves the vaccine response in people with CLL, compared with continuing BTKi treatment as usual. Key secondary outcomes include any impact on quality of life (QoL) and disease activity.

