### Baseline visit

Data on demographic factors (age, sex, ethnicity, height, weight, usual residence (home or residential care)). CLL history (number of lines of therapy, which BTKi is taken and starting dates of therapies), CLL disease activity; bloods taken to measure full blood count (FBC) (haemoglobin, platelet count, lymphocyte count); blood film (presence of prolymphocytes, smear cells or lymphocytosis) and lactate dehydrogenase (LDH) levels; smoking status; self-reported physician diagnosis of comorbidities: diabetes including diet-controlled diabetes, hypertension, ischaemic heart disease, congestive cardiac failure, asthma, chronic obstructive pulmonary disease, high cholesterol, stroke including transient ischaemic attack; current medications; past SARS-CoV-2 vaccines will be collected by the local research team. QoL will be assessed using EORTC-QLQ-CLL17.^32^ Patient global assessment of disease activity will be assessed on a 0–10 NRS for past week using the question:

‘Over the LAST 7 DAYS, in all the ways that your CLL affects you, how would you rate the way you have felt?’ In addition to answering yes or no on whether they have had a temperature greater than 37.5°C, and/or noticed new or enlarged lymph nodes.

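### The models for QoL, disease activity, blood counts and LDH adjust for line of therapy and anti-nucleocapsid status but not for each outcome's own baseline value, which costs precision on the harm question

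*Protocol article*

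**What the plan says.** The statistical analysis text, under Sample size and justification, describes three tiers of analysis.

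- **Antibody outcome.** A "mixed effects regression model, allowing for repeated measures clustered within participants", which is "adjusted for a randomisation factor (first line or subsequent line of therapy), and prior infection status obtained from prevaccination antinucleocapsid antibodies, as fixed effects".
- **Neutralisation and T cell outcomes.** These are handled in a similar way to the antibody outcome.
- **Everything else.** "Other secondary outcomes will be analysed using generalised linear models for binary and continuous data, as appropriate, with model adjustment as described above".

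The abstract (Methods and analysis) lists among the secondary outcomes "participant global assessments of disease activity, blood films, full blood count and lactate dehydrogenase levels, impact on quality of life". These fall in the third tier.

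Baseline values exist for all of them. Under Secondary outcomes, disease activity is a "global assessment using a Numeric Rating Scale (NRS) with 1-week recall at baseline, 3 and 12 weeks PBV". Under Baseline visit, "QoL will be assessed using EORTC-QLQ-CLL17", and the same section lists haemoglobin, platelets, lymphocyte count, blood film and LDH. Table 1 and Sample collection and transport confirm that the bloods are taken at baseline, week 3 and week 12.

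The Introduction shows why these outcomes matter. The hypothesis is that the vaccine response will improve "without significant worsening of the control of the underlying CLL", and "Key secondary outcomes include any impact on quality of life (QoL) and disease activity".

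**The concern.** The covariates for the third tier are fixed by reference to a model built for an antibody response. Under Randomisation, prior infection is justified as a modifier of the serological response to vaccination. No reason is given for using it with quality of life, LDH or blood counts. For those outcomes the natural covariate is the participant's own starting value, and no section names it as a covariate.

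The antibody model might bring baseline in as one of its repeated measures, although the text does not say so. That route is closed to the third tier: those outcomes move to generalised linear models, and only the adjustment is carried across.

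The sample size was set on the antibody outcome alone, so precision on the harm side depends on how the harm outcomes are analysed. When the question is whether pausing treatment makes things worse, a wide interval makes a real worsening easier to miss, and an absence of evidence can reassure more than it should.

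**Working it through.** **Inputs from the document.** Effect size 0.65 SD (0.97 log10 units), 90% power, two-sided 5%, 102 evaluable, 15% missing, 120 randomised (Sample size and justification); 1:1 allocation (Randomisation).

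**Assumed.** The within-arm correlation *r* between an outcome's baseline and follow-up values is not in the document; the range 0.3 to 0.8 is used. The harm outcomes are taken to be as complete as the antibody outcome (51 per arm). The 0.4 SD worsening in the last column is illustrative and is not a stated margin.

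**Step 1. Reproduce the plan's figure.** A two-sample t-test at 0.65 SD, 90% power and two-sided 5% needs 50.7 per arm, so 51 per arm and 102 in total. Allowing for missing data, 102 / 0.85 = 120. Both figures reproduce. The implied SD is 0.97 / 0.65 = 1.49 log10 units. This calculation does not depend on the present point.

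**Step 2. Precision without the baseline covariate.** In SD units, the standard error of the difference is sqrt(2/51) = 0.198. The 95% half-width is 1.984 × 0.198 = 0.393 SD. The difference detectable at 80% power is 0.560 SD from the t-test calculation; the normal approximation, (1.96 + 0.84) × 0.198 = 0.55, agrees closely.

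**Step 3. Precision with the baseline covariate.** Adjusting for baseline multiplies the residual variance by 1 − r², so the standard error, half-width and detectable difference are all multiplied by sqrt(1 − r²).

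| r | sqrt(1 − r²) | CI narrower by | 95% half-width (SD) | Detectable at 80% power (SD) | Power for 0.4 SD worsening |
|---|---|---|---|---|---|
| no baseline term | 1 | – | 0.39 | 0.56 | 52% |
| 0.3 | 0.954 | 5% | 0.38 | 0.53 | 56% |
| 0.5 | 0.866 | 13% | 0.34 | 0.49 | 64% |
| 0.7 | 0.714 | 29% | 0.28 | 0.40 | 80% |
| 0.8 | 0.600 | 40% | 0.24 | 0.34 | 92% |

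**Step 4. Cost of keeping anti-nucleocapsid status.** A simulation of 10,000 trials of 102 participants, with a binary covariate unrelated to the outcome added to a model that already held treatment and line of therapy, gave an empirical standard error of 0.2009 against 0.1999. The ratio is 1.005, a loss of about 0.5%.

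**The case against.** The strongest reply is that this belongs to the statistical analysis plan. The article defers full details to a separate plan, and the sentence at issue is a catch-all that covers binary outcomes as well and is qualified by as appropriate. It does not forbid a baseline term, and the plan may contain one. That limits the point but does not remove it. The article is not silent: it names an adjustment set by reference. A plan that follows it leaves baseline out, and a plan that adds baseline changes what has been published.

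A second reply is that the size rests on an unknown correlation. That is correct, and at r = 0.3 the gain is small.

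A reader might also infer stronger claims that the document does not support.

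- *That the harm comparisons are biased.* Allocation is randomised, so the estimate is unbiased and the 5% error rate holds without baseline adjustment.
- *That chance imbalance could by itself look like a moderate harm.* The 95% limit for imbalance in a baseline value is 1.96 × 0.198 = 0.39 SD, but only about r times that reaches follow-up: 0.12, 0.19, 0.27 and 0.31 SD at r = 0.3, 0.5, 0.7 and 0.8. This variation is already inside the unadjusted standard error.
- *That including prior infection status does damage.* Step 4 puts its cost at about 0.5% of the standard error.
- *That the arms would be compared on raw follow-up values.* Two covariates remain in the model, and the Secondary outcomes list includes change since baseline for participant-rated disease activity. That item does not extend to QoL or the blood tests, and it is not a baseline-adjusted model.

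**Conclusion.** The point holds as a loss of precision on key secondary outcomes. As written, the adjustment for the continuous outcomes outside the immunological group omits their own baseline values, which are collected. At 51 per arm this leaves a detectable difference of about 0.56 SD, where baseline adjustment would give between 0.53 and 0.34 SD for correlations between 0.3 and 0.8. The reading of the text is firm. The size depends on the assumed correlation and on the harm outcomes being about as complete as the antibody outcome.

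The primary outcome, the sample size and the antibody conclusion are untouched. The point does not apply to flare or adherence. It should be corrected because these outcomes carry the risk side of the trial's question and the correction is free.

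**What to change.** Amend the sentence on other secondary outcomes to say that each continuous outcome with a baseline measurement (EORTC-QLQ-CLL17, disease-activity NRS, haemoglobin, platelets, lymphocyte count, LDH) will also be adjusted for its own baseline value, in addition to line of therapy. The baseline should be on the same scale as the outcome, so that if an outcome is log-transformed its baseline is too. Anti-nucleocapsid status may stay or be limited to the immunological outcomes; it makes little difference.

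The cost is one sentence in the analysis plan, with a note that it extends the published adjustment set. It should be settled before the analysis, since the Randomisation section states that the trial statisticians are not blinded. No new data and no change in sample size are needed. If the analysis plan already names these baseline covariates, a statement to that effect closes the point.
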